#### Pain neuroscience education

It includes 4 sessions being organized once a week for 40 to 45 min in person and in each session issues such as neuropathic pain, allodynia, central sensitization, hyperalgesia, peripheral nerve sensitization, neuroplasticity, spreading pain, stress biology, immune response, hypersensitivity, fear, tragedy and pain, and how to cope with pain will be discussed to patient through pictures, terms, and descriptions (Table 2) [12].

**Table 2 Tab2:** The content of neuroscience pain education

1 session	Peripheral neuropathic pain, peripheral nerve sensitization, allodynia, central sensitization, hyperalgesia
2 sessions	Neuroplasticity, spreading pain, central sensitization, hyperalgesia, allodynia
3 sessions	Stress biology, immune response, emotional overload, fear, catastrophization, pain
4 sessions	How to cope with pain?

#### Manual therapy

MT includes 18 sessions of treatment for 6 weeks lasting 60 min each. Soft tissue mobilization, muscle energy techniques, and joint mobilization will be planned to be performed. Soft tissue mobilization includes myofascial stretching for superficial and deep muscles and transverse friction for intervertebral and supraspinal ligaments. Muscle energy techniques include relaxation after isometric contraction for the quadratus lumborum and piriformis muscles that we ask patients to gently contract for 8 s at 30% of maximum voluntary contraction force, and this movement will be repeated after each rest interval. Joint mobilization will be evaluated based on sacroiliac mobility test with standing flexion forward test, Gillet test, and Piedallu Sign test [7, 8].

### Description of the control

Participants in the control group will receive no specific intervention. However, for meeting the ethical codes, we will provide the patients in the control group with a pamphlet included with useful information on taking care during chronic LBP.

### Outcome measures

All the outcome measures explained below were recorded at baseline (pre-test), 2 months post-test, and 4 and 12 months follow-up time points. The flow of the study is also provided in Table 3.

**Table 3 Tab3:** Schedule of enrollment, intervention, study visits, and assessments for all three study groups

Time point	Study period													
	Enrollment	Allocation	Patient-led goal-setting group with PNE				Patient-led goal-setting group with MT				Control group			
			Start	2 m	4 m	12 m	Start	2 m	4 m	12 m	Start	2 m	4 m	12 m
Enrollment														
Eligibility screen	*													
Informed consent	*													
Baseline assessment	*													
Allocation		*												
Intervention														
Patient-led goal-setting group with manual therapy							*	*	*	*				
Patient-led goal-setting group with PNE			*	*	*	*								
Assessments														
Start back			*				*				*			
QBPDS			*	*	*	*	*	*	*	*	*	*	*	*
NRS			*	*	*	*	*	*	*	*	*	*	*	*
SF_36			*	*	*	*	*	*	*	*	*	*	*	*
DASS			*	*	*	*	*	*	*	*	*	*	*	*
PSEQ			*	*	*	*	*	*	*	*	*	*	*	*
FABQ			*	*	*	*	*	*	*	*	*	*	*	*
Tampa Scale			*	*	*	*	*	*	*	*	*	*	*	*
PCS			*	*	*	*	*	*	*	*	*	*	*	*
RNPQ			*	*	*	*	*	*	*	*	*	*	*	*
CSI			*	*	*	*	*	*	*	*	*	*	*	*
Adverse events			*	*	*	*	*	*	*	*	*	*	*	*

*PNE* pain neuroscience education, *MT* manual therapy, *NRS* Numerical Rating Scale, *QBPDS* Quebec Back Pain Disability Scale, *PSEQ* Pain Self-Efficacy Questionnaire, *DASS* Depression Anxiety Stress Scale, *FABQ* Fear Avoidance Beliefs Questionnaire, *TSK* Tampa Scale for Kinesiophobia, *PCS* Pain Catastrophizing Scale, *CSI* Central Sensitization Inventory

#### Demographic data

The sociodemographic data will include gender, age, weight, height, BMI, back pain intensity recorded by the Start Back Questionnaire, LBP history, level of education, and employment situation.

#### Start Back Questionnaire

The Start Back Questionnaire is going to classify patients’ state of pain. The Start Back (9-item version) is a brief validated tool, designed to screen primary care patients with LBP for prognostic indicators that are relevant to initial decision-making [13].

### Primary outcomes

#### Pain intensity

A Numeric Rating Scale (NRS) will be used as a reliable tool (ICC = 0.83) in order to measure pain intensity in eligible patients [14]. NRS will be numbered from 0 to 10, in which patients will rate their pain from 0 (painless) to 10 (worst imaginable pain) [14].

#### Disability

Disability will be assessed using the Quebec Back Pain Disability Scale (QBPDS) (minimum score = 20 and maximum score = 100) [3]. This questionnaire is about how LBP affects people’s daily living, which includes 20 items. The reliability of this questionnaire has been reported by researchers in previous research at different time intervals (ICC = 0.80) [15].

### Secondary outcomes

#### Quality of life

Quality of life is evaluated using the SF-36 questionnaires. SF-36 is a reliable (ICC = 0.80), multipurpose, short-term health survey with 36 questions and is the most widely used public health standard. The scores of each scale vary from 0 to 100, 0 reporting the worst and 100 reporting the best conditions on the scale [16].

#### Depression, anxiety, and stress

To evaluate these psychological outcomes, the Depression Anxiety Stress Scale (DASS) will be used. DASS consists of 21 questions in which each psychological factor is evaluated by 7 questions: depression (range 0–28), anxiety (range 0–20), and stress (range 0–34). A higher score indicates greater intensity. DASS reliability has been observed previously as ICC = 0.88 [17].

#### Self-efficacy

Self-efficacy will be assessed using the Pain Self-Efficacy Questionnaire (PSEQ). This questionnaire is a reliable tool (ICC = 0.82) which includes 10 items. Each item questions the patients’ assessment of their own ability to perform a battery of activities despite pain on a 7-point Likert scale (0 to 6). Higher scores will indicate greater self-efficacy [18].

#### Fear-avoidance beliefs

Fear-Avoidance Beliefs Questionnaire (FABQ) is a 16-item scale describing how much fear and avoidance affect patients, and it also determines what kind of psychosocial interventions are effective for these patients (ICC = 0.90) [19].

#### Kinesiophobia

Kinesiophobia is measured by the reliable Tampa Scale for Kinesiophobia (TSK) (ICC = 0.70). TSK is a 17-item tool, and each item is answered as a 4-point Likert scale. The final score on the scale is between 17 and 68 [20].

#### The Pain Catastrophizing Scale

The Pain Catastrophizing Scale (PCS) is a self-report reliable questionnaire that assesses inappropriate coping strategies and catastrophic thinking about pain and injury (ICC = 0.90). This 13-item scale will be used to assess the range of catastrophic thoughts and behaviors of patients when faced with pain and consists of three subscales of mental rumination, exaggeration, and despair. In previous studies, it shows an average score of 18 in healthy individuals, while in patients with pain, this number is higher and a score of more than 30 has been reported [21].

#### Pain neurophysiology

The Revised Pain Neurophysiology Questionnaire (RNPQ) with 0.84 of ICC will be used for measuring pain neurophysiology. It has 13 items. The scores range from 0 to 13. Higher scores indicate a higher level of neuroscience knowledge [22].

#### Central sensitivity

Central sensitivity will be assessed using the Central Sensitization Inventory (CSI) scale (ICC = 0.91). The CSI includes 25 questions identifying and quantifying the main symptoms associated with Central Sensitivity Syndrome. A score of more than 40 points is reported as a clinical indicator [23].

### Plans to promote participant retention and complete follow-up

To ensure an adequate follow-up rate, the research team will:Maintain regular contact with participants after giving informed consent (regularly every 4 weeks)Ensure contact occurs in the 4 weeks prior to the baseline assessment (pre-test), to ensure greater levels of contact between consent and the intervention startingAfter randomization, participants will be given the opportunity to meet a specific therapist and ask questions prior to the intervention startingParticipants will be reimbursed for their transportation expenses

### Improve adherence to the intervention protocols where an intervention appointment is missed

The research assistant will follow up non-attendees via telephone call to ascertain the reason for non-attendance and whether any assistance from the study team can help in this matter.The research assistant will check if the participant is still willing to continue with the appointed intervention and the study time points outcome measure assessments. In case a participant discontinued the intervention protocol for more than 3 sessions, they would not be included in the analysis.

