## Aims

Primary aim: Investigating the effect of a patient-led goal-setting approach and PNE compared with a patient-led goal-setting approach and MT on pain intensity, disability, and quality of life in patients with chronic LBP.

Secondary aim: Investigating the effect of a patient-led goal-setting approach and PNE compared with a patient-led goal-setting approach and MT on psychological factors in patients with chronic LBP.

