### Description of the interventions

#### Patient-led goal-setting approach

The intervention will be carried out for 8 weeks including 5 face-to-face sessions. The first session takes about 1 h, and the other sessions are held for 15 to 30 min with 2-week intervals. Then, two follow-up sessions (lasting 30 min each) will be developed with a 1-month interval; furthermore, one session will be organized 12 months after the first session, and finally, the results will be collected. The SMART model will be used for applying this intervention. This model includes a special process for goal setting that is measurable, achievable, and associated to a specific time return. In this model, the researcher is trained in setting goals by the patient, considers the patient’s history of LBP, and discusses about the issue that led to the occurrence of LBP [4]. Patients are asked to prioritize these problems based on what they want to focus on. Then, the strategies are discussed based on evidence-based guidelines, and the patient sets specific goals and strategies to work independently between sessions. Patients record their set goals, progress towards these goals, and agree on strategies for achieving the goal in their workbooks. If the goal strategies include consultation with a health care professional, the patient is encouraged to pursue this independently (Table 1) [3–5].

**Table 1 Tab1:** Components of the interventions

Patient-led goal-setting intervention
Session 1: week 1
► Orientation of patient
► SMART approach explained
► Goals and strategies developed
Homework task: review educational material
Session 2: week 3
► Education and discussion
► Review of goals, progress towards, and barriers to achieving goals
► Strategies developed
Sessions 3 and 4: weeks 5 and 7
► Review of goals, progress towards, and barriers to achieving goals
► Strategies developed
Session 5 (completion of the intervention): 2 months
► Review of goals, progress towards, and barriers to achieving goals
► Strategies developed
► Outcomes measured
Post-intervention follow-up (3 months)
► Review of goals, progress towards, and barriers to achieving goals
Post-intervention follow-up (4 months)
► Review of goals, progress towards, and barriers to achieving goals
► Outcomes measured
Post-intervention follow-up (12 months)
► Outcomes measured

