### Statistical analysis

The data will be summarized with descriptive statistics (mean, median, standard deviation, percentiles for numerical variables, frequencies and percentages for categorical variables). The SPSS software version 26 will be used to analyze the data. The Shapiro–Wilk test will be used to examine the normal distribution of data. If the normal distribution is approved, the mix model ANOVA will be used to compare the differences in scores related to each variable in the pre-test and post-test in each group (with-in group effects) and to examine the differences between groups in each time point (between group effects), and Bonferroni post hoc test will be used to find significant differences and compare the groups. This model allows for possible missed data. We will assume data missing at random. Study group and time of assessment will be used as fixed factors and patients will be used as random factors. Otherwise, the Mann–Whitney *U* test will be used to compare two independent groups in case the normal distribution was not approved. Finally, after post hoc tests, the Cohen test (*d*) will be used in order to calculate the effect size [24]. *P*-value < 0.05 will be considered significant. The main conclusion will be drawn from the unadjusted analysis without performing any subgroup analysis of primary and secondary outcomes.

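### Participants who discontinue more than 3 sessions are removed from the analysis, under one threshold applied to arms with 9, 23 and 0 scheduled sessions

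*Protocol article*

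**What the plan says.** The section on missed intervention appointments has the research assistant telephone non-attenders and check whether they will continue with the intervention and with the outcome assessments. It then sets the rule: "In case a participant discontinued the intervention protocol for more than 3 sessions, they would not be included in the analysis".

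The scheduled contacts differ by arm:

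- Goal setting, given in both active arms (Patient-led goal-setting approach): "The intervention will be carried out for 8 weeks including 5 face-to-face sessions".
- PNE (Pain neuroscience education): "It includes 4 sessions being organized once a week for 40 to 45 min in person".
- MT (Manual therapy): "MT includes 18 sessions of treatment for 6 weeks lasting 60 min each".
- Control (Description of the control): "Participants in the control group will receive no specific intervention".

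On missing data, the Statistical analysis section says of the mixed model: "This model allows for possible missed data. We will assume data missing at random". The primary aim, under Aims, is the comparison of the two active arms. The Discussion adds comparisons with control.

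**The concern.** Attendance is observed after randomisation and can depend on the treatment received and on how the participant responds to it. Selecting on it means that the groups compared are no longer the groups that were randomised. Here the selection also cannot work equally across arms, because the same count of sessions is a large part of one programme, a small part of another, and impossible to reach in the third. The stated primary comparison and both comparisons with control are affected.

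The rule also works against the chosen model. A mixed model under missing at random is useful because a participant with incomplete data still contributes whatever was observed. The rule deletes the whole participant, including the baseline and any follow-up already collected. Some non-attenders may have complete outcomes, since staff are told to ask whether they will continue with assessments.

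**Working it through.** The plan gives no attendance or exclusion figure, so there is none to reproduce. The sample size section allows for 10% loss to follow-up and mentions no allowance for adherence exclusions.

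**Step 1. Sessions per arm (from the documents)**

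- Goal setting + PNE: 5 + 4 = 9
- Goal setting + MT: 5 + 18 = 23
- Control: 0

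More than 3 sessions means at least 4. That is 4/9 = 44% of the PNE-arm programme and 4/23 = 17% of the MT-arm programme. It cannot occur in control. If sessions are counted in total, a participant attending 19 of 23 MT-arm sessions is removed, while one who misses 3 of the 4 PNE sessions and nothing else is kept. This step needs no attendance rate.

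**Step 2. Share excluded if misses are counted in total**

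Assumptions, none of them in the documents: each session is missed with probability p, equal in both active arms and independent between sessions. Then

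P(excluded) = 1 − Σ (k = 0 to 3) C(n,k) p^k (1−p)^(n−k).

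At p = 0.10:

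- n = 9: 1 − (0.3874 + 0.3874 + 0.1722 + 0.0446) ≈ 0.008
- n = 23: 1 − (0.0886 + 0.2265 + 0.2768 + 0.2153) ≈ 0.193

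| Miss rate p | PNE arm (9) | MT arm (23) | Control |
|---|---|---|---|
| 5% | 0.06% | 2.6% | 0% |
| 10% | 0.8% | 19.3% | 0% |
| 15% | 3.4% | 46.0% | 0% |
| 20% | 8.6% | 70.4% | 0% |

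If the 105 participants are split equally (35 per arm; no ratio is stated), the 10% row is about 0.3 and 6.7 participants, and the 5% row is less than one MT participant.

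**Step 3. Other readings at a mean miss rate of 10%**

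| Reading | PNE arm | MT arm |
|---|---|---|
| Only PNE or MT sessions count (4 vs 18) | 0.01% | 9.8% |
| 3- and 4-month goal reviews also count (11 vs 25) | 1.9% | 23.6% |
| Miss rate varies between participants (beta-binomial, concentration 5; 9 vs 23) | 6.4% | 24.3% |
| Four consecutive sessions needed (9 vs 23) | 0.05% | 0.2% |

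For the consecutive reading, P(run of 4) ≈ p⁴[1 + (n − 4)(1 − p)]. This gives 0.0001 × (1 + 5 × 0.9) = 0.00055 for n = 9 and 0.0001 × (1 + 19 × 0.9) = 0.0018 for n = 23.

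In every row the MT arm loses more than the PNE arm. The size ranges from negligible to large.

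**Step 4. What this could do to a comparison**

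If a share e is removed from an arm, and retained and excluded participants differ by δ on average, the arm's mean shifts by e × δ. With δ = 0.5 SD (assumed) and misses counted in total, the MT versus PNE contrast shifts by:

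- 10% miss rate: (0.193 − 0.008) × 0.5 ≈ 0.09 SD
- 15% miss rate: (0.460 − 0.034) × 0.5 ≈ 0.21 SD

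MT versus control shifts by 0.193 × 0.5 ≈ 0.10 SD and 0.460 × 0.5 = 0.23 SD. The sign follows the sign of δ, which the documents do not give.

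**The case against.** **The rule is ambiguous.** It speaks of discontinuing for more than three sessions and does not say whether scattered absences add up. If it means four consecutive sessions, independent misses at 10% would trigger it in well under 1% of either arm. This stands. It limits any statement of size, but it does not make the rule equal across arms or remove the exclusion.

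**The exclusion rates are not known.** A reader might infer that the arms will lose participants at very different rates. The documents support only a difference in opportunity; no attendance data are given, and at a 5% miss rate the loss is small even when misses are totalled.

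**The direction is not known.** A reader might infer that the rule flatters MT. That follows if poor responders stop attending. If participants stop because they have recovered, removing them makes MT look worse.

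**The two provisions do not contradict each other.** One sets who is analysed, the other how gaps are handled among those analysed, and both can be carried out as written. The fair statement is that the exclusion defeats the purpose of the model.

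**Analyst blinding need not be broken.** A reader might infer that applying the rule reveals the arm to the blinded analyst. The research assistant follows up non-attendance, and someone other than the analyst can apply the rule before a coded dataset is passed on.

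**An analysis plan not shown might define an all-randomised set.** That would answer a gap. Here the article does not leave the matter open: it states an exclusion from the analysis, without confining it to a per-protocol or supportive set.

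**Conclusion.** The point holds and should be corrected before the analysis. The plan as written removes randomised participants for what happens after allocation, by a count that bears unequally on arms with 9, 23 and 0 sessions, and it names no analysis that keeps them. That conclusion rests on the text and on the session counts alone.

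The size is conditional. With equal, independent misses counted in total, exclusions in the PNE and MT arms run from 0.06% and 2.6% (5% miss rate) to 3.4% and 46% (15%). Under a consecutive-session reading they are about 0.05% and 0.2% at 10%. The bias in PNE versus MT, or in either comparison with control, cannot be signed or sized from the documents, and so could not be corrected for afterwards.

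**What to change.** Delete the exclusion from the main analysis. In its place, state that all randomised participants are analysed in their allocated group, with every available outcome entering the mixed model regardless of attendance, and that non-attenders continue to be invited to the scheduled outcome assessments.

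If an adherence-based analysis is wanted, label it as supportive. Define it as a proportion of the sessions scheduled in that arm, and say which sessions count and whether absences are totalled or must be consecutive.

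The cost is a short change of text and minor effort to keep collecting outcomes that are already scheduled. The estimate will then describe treatment as assigned rather than as fully received; the supportive analysis can speak to the latter, with its selection acknowledged.

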### Sample size estimation

Sample size has been estimated via G*Power 3.1.9.4 based on the therapy effects on pain and accounting for a 10% loss to follow-up after 4 and 12 months. An a priori power analysis was performed considering full factorial repeated measures and using a small effect size (Cohen’s *d*) of 0.25, confidence level (*α* = 0.05), and desired power (95%). The required sample size was calculated as 15 participants per group. Table 3 provides a schedule of enrollment, intervention, study visits, and all the assessments performed for all three study groups.

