**Methods:**

A total of 105 patients suffering from chronic LBP will be recruited via flyers displayed in hospitals and universities, and those meeting the study’s criteria will randomly be allocated into a patient-led goal-setting approach with the PNE group, and/or with the MT program group, and/or a control group. The primary outcomes will be the pain intensity and disability. Secondary outcomes include quality of life, depression, anxiety and stress, fear avoidance beliefs, kinesophobia, pain self-efficacy, catastrophic pain, neurophysiology of pain, and central sensitivity. All the outcomes will be recorded at 2 months after receiving the treatment as post-test sessions and after 4 and 12 months as follow-up sessions. The Ethics Committee in Research at Sport Sciences Research Institute of Iran approved the protocol of this trial (IR.SSRC.REC.1400.084). Written, informed consent to participate will be obtained from all participants. All methods will be conducted in accordance with the ethical standards of the Declaration of Helsinki and in accordance with relevant guidelines and regulations. We will disseminate the findings through peer-reviewed publications and conference presentations and send them to the participants.

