## Discussion

The aim of this study will be to compare the effect of patient-led goal-setting approach combined with PNE or MT in patients with chronic LBP. The main question of this study is whether the patient-led goal-setting approach combined with PNE is more effective than MT in reducing pain intensity related with chronic LBP. Further objectives will be also to assess the effect of these two interventions on disability, quality of life, and psychosocial factors in chronic LBP compared to a control group. A total of 105 patients will participate in this study and the athletic trainer who performs the pre-test and post-test as well as follow-up evaluations will be blinded to the participants’ group code. It is expected that this RCT will provide novel data on the effectiveness of the patient-led goal-setting approach combined with PNE or MT in patients with chronic LBP compared to a control group.

In the current study, we will evaluate the effects of combined interventions on psychological outcomes as well as central sensitivity. It is expected that this prospective trial may contribute towards refining guidelines for good clinical practice and may be used as a basis for health authorities’ recommendations. If successful, the findings and information provided by this study will potentially have implications for physiotherapists, athletic trainers, and health care practitioners.

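### The stated effect size, power and 15 per group do not fit together, do not lead to 105 patients, and do not give 95% power for the PNE-versus-MT comparison at d = 0.25

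*Protocol article*

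**What the plan says.** Under Sample size estimation, the article reports a G*Power calculation for pain, "considering full factorial repeated measures and using a small effect size". The effect is given as "using a small effect size (Cohen’s *d*) of 0.25", with alpha 0.05, 95% power and an allowance of 10% for loss to follow-up. The result is: "The required sample size was calculated as 15 participants per group". The section names neither the ANOVA effect that was powered nor the correlation between repeated measurements.

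The enrolment figure is different. The abstract states: "A total of 105 patients suffering from chronic LBP will be recruited". Eligibility criteria and Discussion also give 105. Study design and setting describes three arms, and Outcome measures sets four time points (baseline, 2, 4 and 12 months).

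The Discussion defines the target comparison: "The main question of this study is whether the patient-led goal-setting approach combined with PNE is more effective than MT in reducing pain intensity". The Aims section gives the same two-arm contrast as the primary aim. Statistical analysis plans a mixed-model ANOVA with Bonferroni post hoc comparisons between groups.

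**The concern.** Three things do not fit. First, 15 per group is far too few for 95% power at a d of 0.25 under ordinary assumptions, so either the label or the number is wrong. Second, three groups of 15 make 45, and a 10% allowance cannot turn 45 into 105. Third, a calculation built on a repeated-measures ANOVA across three arms does not show what the trial can do for its declared main question, which concerns two of those arms.

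At stake is how the result is read. Someone who takes the paragraph at face value would believe that a small effect is covered with 95% power, and could read a null PNE-versus-MT result as good evidence against a small difference. The trial would not provide that evidence.

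**Working it through.** **Inputs from the article.** k = 3 groups; m = 4 measurements; alpha = 0.05; power 0.95; effect 0.25; loss 10%; 15 per group; 105 in total.

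**Assumed, because not stated.** Correlation rho = 0.5 and sphericity (other correlations shown below); equal allocation, so 105/3 = 35 per group; two-sided pairwise tests.

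**1. Reproducing 15 per group.** For the within-between interaction, power comes from a noncentral F with lambda = f² × N × m/(1 − rho), df1 = (k − 1)(m − 1) and df2 = (N − k)(m − 1).
- f = 0.25, N = 45: lambda = 0.0625 × 45 × 4/0.5 = 22.5, df = 6 and 126, power 0.955.
- f = 0.25, N = 42: lambda = 21.0, df = 6 and 117, power 0.939.

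The smallest equal-group total is therefore 45, which is the printed 15 per group.

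**2. The same test with 0.25 taken as d.** The usual two-group conversion is f = d/2 = 0.125.
- N = 45: lambda = 0.015625 × 45 × 4/0.5 = 5.625, power 0.36.
- 95% power needs N = 171. At N = 105 power is 0.77.
- N = 45 is reached only if rho is about 0.88.

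These figures depend on how d is turned into an interaction f. If two arms are equal at baseline and then differ by a constant delta, f = 0.2165 × delta. So d = 0.25 gives f of about 0.05, the required total is roughly 900 to 1,000, and power at N = 45 is about 9%. No conversion brings d = 0.25 near 15 per group at rho = 0.5.

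**3. From 15 per group to 105.**
- 3 × 15 = 45.
- If loss is still to be added: 45/0.9 = 50, or 15/0.9 = 16.7, rounded up to 17 per group and 51 in total.
- Falling from 105 to 45 would take a loss of (105 − 45)/105 = 57%, against the stated 10%.
- Under the settings of step 1, 45 is the figure before loss: 40 to 41 completers would have 92.5% to 93.3% power.

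**4. PNE versus MT at d = 0.25, one visit, unadjusted.** Noncentral t with parameter d × √(n/2) and 2n − 2 df. After 10% loss, 35 × 0.9 = 31.5, taken as 31.

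| n per group | alpha 0.05 | alpha 0.05/3 |
|---|---|---|
| 35 | 0.178 | 0.086 |
| 31 | 0.162 | 0.076 |

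For 95% power at alpha 0.05, 417 per group are needed.

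**5. What 105 does deliver for PNE versus MT, with 31 evaluable per group.**
- Single visit, unadjusted, 80% power: d of about 0.72 (0.84 with Bonferroni over three pairs).
- Average of the three post-baseline visits, adjusted for baseline, with equal correlations: the variance factor is (1 + 2rho)/3 − rho². At rho = 0.5 it is 0.417 (square root 0.646), so 0.72 × 0.646 = 0.47. At rho = 0.7 it is 0.31 (square root 0.557), so 0.72 × 0.557 = 0.40.
- On that averaged analysis, d = 0.25 is equivalent to 0.25/0.646 = 0.39 or 0.25/0.557 = 0.45 in the t test above. Power is about 32% and 41%, before any Bonferroni correction.

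**The case against.** Several points on the other side are sound and limit what may be concluded.

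- A reader might infer that 15 per group arises only if 0.25 is Cohen's f for the six-degree-of-freedom interaction. The article does not support that certainty, since it states neither the effect tested nor the correlation. f = 0.125 with rho of about 0.88 also gives 45, and so does a time-effect test with three measurements at f = 0.25 and rho = 0.5. The f reading is the most natural because it matches the documented four time points at a conventional correlation, but it remains an inference.
- A reader might infer that the trial can detect only a large PNE-versus-MT difference. That describes an unadjusted single-visit test. The planned model uses all visits, and step 5 shows that a moderate difference is within reach under an averaged, baseline-adjusted reading. However, the article says that its main conclusion rests on the unadjusted analysis, so this gain cannot be taken for granted.
- A reader might infer that the article promises 95% power for PNE versus MT. It does not say so. It attaches 95% power to a repeated-measures analysis and names the main question elsewhere. Powering the ANOVA is common in three-arm trials. If 0.25 is f, the interaction test at N = 105 has more than 99.9% power.
- A reader might infer that the trial is under-recruited against its own target. It is not: 105 exceeds 45 and 51. The text also says that loss was accounted for, so 15 may be meant to include it. The gap is an unexplained excess.

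None of this makes a small d of 0.25 with 95% power yield 15 per group under ordinary assumptions, or connects that number to 105.

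**Conclusion.** The sample-size statement is wrong as written and should be corrected. Without any assumption, the printed 15 per group and the planned 105 disagree, and the 10% loss does not bridge them. With rho = 0.5, 15 per group corresponds exactly to f = 0.25 for the interaction. Read as d = 0.25 (f = 0.125), the same 45 patients have 36% power, and less under a constant post-baseline difference. A mislabelled metric is the likeliest explanation, but it is not proven. Where 105 came from cannot be established: f = 0.125 with rho = 0.7 would give it, and so would f = 0.16 with rho = 0.5, but the article states neither.

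For the declared main question, 95% power at d = 0.25 does not hold at the planned size. Power is 16 to 18% for a single unadjusted visit and 8 to 9% with Bonferroni over three pairs, assuming equal allocation. Averaging visits with baseline adjustment raises it but leaves it well below 95%. The shortfall applies to effects of this size; differences near one standard deviation are well covered.

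**What to change.** Rewrite the paragraph under Sample size estimation so that it:

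1. states the effect metric actually entered (f or d), the ANOVA effect powered, the number of measurements and the correlation;
2. says whether 15 per group is before or after the 10% loss, and explains how the trial came to 105;
3. removes the claim of 95% power for a small d of 0.25;
4. states what 105 delivers for PNE versus MT on pain under the planned analysis. For example: about 31 evaluable per group give 80% power at two-sided 5% for d of about 0.72 at a single visit unadjusted (0.84 with Bonferroni), or for roughly 0.40 to 0.47 on the baseline-adjusted average of the three post-baseline visits, at an assumed correlation of 0.7 to 0.5. The figure quoted should match the analysis that will carry the main conclusion.

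The sponsor should confirm the metric from its own G*Power record and not adopt f = 0.25 because it happens to fit. No extra enrolment or design change is requested. The only cost is a less favourable stated power.
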